### Diagnostic methods

We will provide either multiplex PCR tests or mNGS (including examination of both DNA and RNA) for microbiological examinations in this study. According to recommendations, we will include HSV types 1 and 2; *Varicella zoster virus*, *Enteroviruses*, *Neisseria meningitidis* and *Streptococcus pneumoniae* [14]. The autoimmune antibody spectrum will be established over several admission days as the disease progresses (Table 2).

**Table 2 Tab2:** The detailed autoimmune antibody spectrum of each sampling day

Admission days	Samples	Methods	Antibody spectrum
Day 0	Blood and CSF	CBA and TBA	NMDAR, GABABR, LGI1, Caspr2, AMPAR1, AMPAR2, GAD, MOG
Day 7	Blood and CSF	CBA and paraneoplastic antibody OR TBA	NMDAR, LGI1, GABABR, CASPR2, AMPAR1, AMPAR2, IgLON5, DPPX, GAD65, mGluR5, GlyR, D2R Paraneoplastic antibody: Hu, Yo, Ri, CV2(CRMP5), Ma1, Ma2, Amphiphysin, SOX1, Tr (DNER), Zic4, GAD65, PKCγ, Recoverin, Titin
Day 14	Blood and CSF	CBA	MDAR, GABABR, LGI1, Caspr2, AMPAR1, AMPAR2, GAD, MOG
Day 15–60	Blood and CSF	CBA ± TBA	MDAR, GABABR, LGI1, Caspr2, AMPAR1, AMPAR2, GAD, MOG
1/3/6/12 months	Blood	CBA	Re-examinations for autoimmune-positive patients

### Duration of follow-up

Follow up will take place on the 7th and 14th day and in the 3rd, 6th and 12th month of the trial. Follow-up examinations will mainly consist of clinical evaluation, physical examination, routine blood examinations including routine blood parameters, C-reactive protein, D-dimer, and synchronized glucose; CSF examinations such as pressure, biochemical and routine tests; nervous system analysis scores including mRS, GOS Score and EQ-5D; extra autoimmune encephalitis antibody tests and molecular etiology examination.

According to these examinations, if symptoms persist or the condition of the participant is worse between the 15th and 60th day, we may reperform additional autoimmune encephalitis antibody tests and molecular etiology examinations (mNGS test).

In summary, detailed follow up examination will proceed in the following order; clinical evaluation, physical examination and nervous system analysis scores should be evaluated on the 7th and 14th day of the trial. In addition, a lumbar puncture and routine blood examination should also be conducted on these days, and CSF will be subjected to autoimmune encephalitis antibody tests (Table 2). Assessments in the 3rd and 12th month will involve clinical evaluation, physical examination, and nervous system analysis scores.

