**Methods:**

IMPROVE is a multicenter, open label, randomized controlled clinical trial that aims to evaluate the diagnostic performance, applications, and impact on patient outcomes of a new diagnostic algorithm that combines metagenomic next-generation sequencing (mNGS), multiplex polymerase chain reaction (PCR) and autoimmune antibody testing. The enrolled patients will be grouped into two parallel groups, multiplex PCR test plus autoimmune antibody group (Group I) or the mNGS plus autoimmune antibody group (Group II) with a patient ratio of 1:1. Both groups will be followed up for 12 months. The primary outcomes include the initial time of targeted treatment and the modified Rankin scale score on the 30th day of the trial. The secondary outcomes are the cerebrospinal fluid index remission rate on the 14th day, mortality rate on the 30th day, and an evaluation of diagnostic efficacy. The two groups are predicted to comprise of 484 people in total.

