### Assessment and analysis of outcomes

The primary and secondary outcomes between Group I and Group II will be compared. Primary outcomes are the initial time of targeted treatment and mRS score on the 30th day whilst secondary outcomes include CSF index remission rate on the 14th day, mortality rate on the 30th day, and the evaluation of diagnostic efficacy. Through these assessments, we may explore the best diagnostic algorithm for encephalitis/meningitis, and finally determine its optimal treatment.

The results for the trial outcomes will be analyzed through the following methods. First, we will review whether the enrolled cases meet the selection and exclusion criteria, and whether the actual number of enrolled, excluded and dropped cases in each center are accounted for at the end of the study; we will then perform a comparability analysis. Data relating to demographic characteristics, general and baseline (before the test) conditions will be compared between the two groups. The statistical analyses to be employed include two-sided t-tests, Wilcoxon tests, and chi-square tests—which will compare the outcomes between the two groups. A P value ≤ 0.05 was considered statistically significant. Excel was adopted for the management of data and the performance of statistical analysis after verification. SPSS 11.0 and PRISM 9.0 were the software used for statistical analyses.

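### A primary outcome is the mRS on day 30, but the printed follow-up schedule contains no day-30 assessment of all patients

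*Protocol article*

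**What the plan says.** The outcome is stated twice with the same time point. The Methods section on assessment and analysis of outcomes reads: "Primary outcomes are the initial time of targeted treatment and mRS score on the 30th day". The abstract agrees: "the modified Rankin scale score on the 30th day of the trial". The secondary outcomes include "mortality rate on the 30th day, and the evaluation of diagnostic efficacy".

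The visit list is equally explicit. The section on duration of follow-up opens: "Follow up will take place on the 7th and 14th day and in the 3rd, 6th and 12th month of the trial". It says what is done at these visits, including "nervous system analysis scores including mRS, GOS Score and EQ-5D". Its closing paragraph restates the timing in two parts: "nervous system analysis scores should be evaluated on the 7th and 14th day of the trial", and "Assessments in the 3rd and 12th month will involve clinical evaluation, physical examination, and nervous system analysis scores".

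Two further contacts are described. In Table 2 (section on diagnostic methods), the last row has a blood test at 1, 3, 6 and 12 months, labelled "Re-examinations for autoimmune-positive patients". Both the follow-up section and Table 2 also allow repeat testing between days 15 and 60, which the follow-up section ties to ongoing or worsening illness.

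**The concern.** The outcome definition and the visit list do not meet. A centre that follows the schedule as printed scores the mRS on days 7 and 14 and then not again until the third month, so no visit produces the day-30 score for all patients.

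That score is one of two primary outcomes, and functional status on a given day cannot be recovered from a later visit. If it is recorded only where a patient happens to be seen around day 30, the patients with a score are a selected group. If a neighbouring visit is used instead, a different outcome is analysed. In an open-label trial, leaving that choice until after the data are in is best avoided.

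**Working it through.** The article gives no figure to reproduce on this point. The check sets every contact it describes against day 30.

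**Scheduled for all patients (section on duration of follow-up)**

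| Contact | mRS described? | Distance from day 30 |
|---|---|---|
| Day 7 | yes | 30 − 7 = 23 days before |
| Day 14 | yes | 30 − 14 = 16 days before |
| 3rd month | yes | 31 to 60 days after |
| 6th month | yes in the opening list; not repeated in the closing paragraph | later still |
| 12th month | yes | later still |

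The range for the third month depends on how it is read. If it means the third month in progress, it runs from about day 61 to day 90, which gives 61 − 30 = 31 to 90 − 30 = 60 days. If it means three months completed, it is about day 90, which gives 60 days. The article states no visit window, so I carry the range.

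**Contacts for some patients only**

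| Contact | Who | What is recorded | Closes the gap? |
|---|---|---|---|
| 1-month row of Table 2 | autoimmune-positive patients | cell-based antibody assay on blood | No: selected patients, no mRS mentioned |
| Retesting, days 15 to 60 | patients whose symptoms continue or who deteriorate; optional | antibody tests and mNGS | No: selected patients, no mRS mentioned, day not fixed |

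The second of these is triggered by a poor clinical course. Any mRS noted at such a contact would come from patients doing worse than the rest.

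**Can the day-30 score be filled in later?** The section on data collection and quality management requires the clinician to complete the form while questioning the participant in person, and excludes completing it afterwards from memory. A day-30 mRS reconstructed at the third-month visit would not fit that rule.

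**Can day-30 mortality be obtained without a day-30 visit?** Largely yes. Both groups are followed for 12 months, so a date of death learned in hospital or at the third-month visit settles whether the patient was alive on day 30. The exception is a patient lost to follow-up between day 14 and the third month. The article does not say that mortality will be derived this way.

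**The case against.** The strongest objection is that this is a condensed journal article. Full visit schedules usually stand in the complete protocol and the case report form, and neither is at hand. Fig. 1, to which the study design section refers for the detailed schematic, was not available to this review and may show a day-30 visit. The follow-up section is also loosely drafted: month 6 is in its list but missing from its own summary, and Table 2 uses a series that does include one month. A drafting omission is quite plausible.

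Part of this stands. A reader might infer that the day-30 mRS will not be collected, or will be collected only in inpatients and antibody-positive patients. The documents do not support that: they show that the printed schedule omits it, not what centres will do. Nor do they say that day-14 scores will be carried forward or month-3 scores taken back. Those are risks of leaving the gap open, not plans.

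A reader might also put day-30 mortality on the same footing as the mRS. That goes too far, because vital status on day 30 follows from a date of death. It would likewise be wrong to call the month-1 blood test the only contact near day 30, since the conditional retesting spans it.

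The objection does not remove the contradiction. The article did not leave the schedule to another document. It printed a list, partly repeated it, and left out the time point of a primary outcome. If Fig. 1 does show day 30, the follow-up section conflicts with the figure and still needs correcting.

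**Conclusion.** The point holds as an internal contradiction that must be resolved. Followed as written, the trial schedules no mRS for all patients on day 30, although that score is a primary outcome. The schedule applies to all 484 planned patients. The nearest scheduled scores are 16 days too early or about one to two months too late (31 to 60 days), and the two other contacts near day 30 cover selected patients without a stated mRS.

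The conclusion rests on the text alone, with Fig. 1 and the full protocol unseen, and on reading the third month as somewhere between about day 61 and day 90. The size of any resulting bias cannot be given, because the article does not say how many patients would be seen near day 30. For mortality the point is minor: the plan should say that day-30 status is derived from dates of death.

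**What to change.** Reconcile the section on duration of follow-up with the section on assessment and analysis of outcomes:

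- Add a day-30 assessment to the visit list and to its summary paragraph, with a stated window. It should record mRS and vital status for every randomised patient, whatever the diagnosis and whether or not the patient has been discharged.
- State that a day-14 or month-3 mRS does not substitute for the day-30 score.
- State that day-30 mortality is taken from recorded dates of death, with vital status confirmed at the new assessment.
- If assessment by telephone is to be allowed, amend the face-to-face rule in the section on data collection and quality management to match. Otherwise the new assessment would breach it.
- Check Fig. 1 and the case report form against the corrected list.

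Moving the outcome to an existing visit would also remove the contradiction, but it would change a primary outcome. Adding the assessment keeps the outcome as defined in both the abstract and the Methods. The cost is one short assessment per patient and one case report form page.

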### Sample size calculation

The predicted sample size was calculated using the PASS 11 software. Assuming hazard ratio (HR) = 1.48 and θ = 1, and according to previous research, pE = 0.7, PA = 0.5, each group requires 230 samples. Assuming a 5% drop-out rate in follow-up, each group needs 230 × 1.05 = 242 people; therefore, the total sample size of the two groups combined is calculated to be 484 people.

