## Methods

### Study design

This study is a multicenter open label, randomized controlled clinical trial of non-inferiority with two arms recruiting patients with suspected encephalitis/meningitis. The enrolled patients will be grouped into two parallel groups with a ratio of 1:1, those whose diagnoses were achieved through multiplex PCR tests plus autoimmune antibody analyses (Group I), and those being assessed through the use of mNGS plus autoimmune antibody testing (Group II). The detailed study schematic is shown in Fig. 1.

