### Study flowchart and clinical evaluation of enrolled patients

Adult patients who meet the inclusion criteria will be eligible (Table 1). Eligible patients with suspected encephalitis/meningitis will be included after signing the informed consent forms. As outlined above, the participants will be randomly assigned in a 1:1 ratio to Group I or Group II. The randomization is performed through the online central randomization system stratified by the study sites (Clinflash, China). To facilitate autoimmune encephalitis antibody tests and molecular etiological examinations, 13 ml of peripheral blood and 8 ml of cerebrospinal fluid (CSF) will be collected. The first screen will include basic patient characteristic, as well as additional information such as present history, functional assessments (modified Rankin Scale [mRS], Glasgow outcome score [GOS] and EuroQol-5 Dimension (EQ-5D)), physical examinations, cranial magnetic resonance imaging (MRI), blood examinations including routine blood tests, C-reactive protein, synchronous glucose, D-dimer, *Treponema pallidum* particle agglutination assay/rapid plasma reagin, thyroid hormones and thyroid-related antibodies; CSF pressure, biochemical and routine tests; and etiological examinations of CSF including latex agglutination test, ink stain, and bacterial, fungi and tuberculosis cultures. Electroencephalograms are to be performed according to clinical necessity.

**Table 1 Tab1:** Inclusion and exclusion criteria

Inclusion criteria
• Aged from 18 to 80 years old
• Without clear diagnosis
• Without effective antimicrobial therapy
• The suspected meningitis/encephalitis patients should meet the ① or ② items as following:
① Suspected meningitis: Rapid onset fever (> 38.5 °C). with at least one of the three manifestations as following:
(1) Neck stiffness
(2) Alteration of consciousness
(3) Other signs indicating meningitis, for example, meningeal irritation sign
② Suspected encephalitis: Altered consciousness because of unidentified reasons that persisted for longer than 24 h, including lethargy, irritability, or a change in personality, and have at least one of these manifestations:
(1) Fever or history of fever (≥ 38 °C, oral temperature) during the presenting illness
(2) Seizures not explained by a previously known seizure disorder
(3) CSF pleocytosis (white blood cell count of more than 4 cells per μl)
(4) Electroencephalographic (EEG) findings indicative of encephalitis

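### The figure of 230 per group does not follow from the stated inputs at a 5% level with 80, 85, 90 or 95% power; a total was probably reported as a per-group number, which the sponsor must confirm

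*Protocol article*

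**What the plan says.** The section Sample size calculation gives the whole basis in a few lines. The software is named: "The predicted sample size was calculated using the PASS 11 software". The inputs follow: "Assuming hazard ratio (HR) = 1.48 and θ = 1", then "pE = 0.7, PA = 0.5, each group requires 230 samples". Drop-out of 5% is added as "each group needs 230 × 1.05 = 242 people", and doubling gives the enrolment target of 484.

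The section does not say what θ, pE and PA stand for. It names no endpoint, formula, significance level, sidedness or power, and power is mentioned nowhere else in the article.

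Three other statements bear on the calculation:

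- Allocation: "the participants will be randomly assigned in a 1:1 ratio to Group I or Group II" (Study flowchart and clinical evaluation of enrolled patients).
- Tests and level: "The statistical analyses to be employed include two-sided t-tests, Wilcoxon tests, and chi-square tests", and "A P value ≤ 0.05 was considered statistically significant" (both in Assessment and analysis of outcomes). The level is not tied to the sample size.
- Hypothesis: the trial is a "randomized controlled clinical trial of non-inferiority with two arms" (Study design). No margin is given.

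**The concern.** A hazard ratio, a θ of 1, a pE and a PA together are the parameters of the Cox sample size formula. In that formula pE is the overall probability of an event, PA is the proportion of patients in one arm (0.5 fits the 1:1 allocation), and θ is the null hazard ratio. The formula returns the number of patients in both arms together, yet the article attaches its result to each group and then doubles it.

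If that is what happened, the target of 484 is not the number the calculation supports. As the text stands, a reader cannot tell what power the trial has, for which endpoint, or what a null result would exclude. The size also needs a clear basis because each participant gives extra blood and CSF for the study.

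**Working it through.** **Inputs.** HR = 1.48, θ = 1, pE = 0.7, PA = 0.5 and 230 per group come from Sample size calculation. The 5% level comes from Assessment and analysis of outcomes. Sidedness and power for the calculation are not stated, so both are assumptions and are varied below.

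**Step 1: try to reproduce 230.**

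N(total) = (z_α + z_power)² / [PA(1 − PA) · pE · (ln HR − ln θ)²]

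ln 1.48 = 0.3920 and its square is 0.1537. The denominator is 0.25 × 0.7 × 0.1537 = 0.02690.

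At one-sided 5% and 80% power: (1.645 + 0.842)² = 6.183, and 6.183 / 0.02690 = 229.9. The figure 230 is reproduced, but as a total (115 per group).

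**Step 2: other settings on the same reading.**

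| Level | Power | Total N | Per group |
|---|---|---|---|
| One-sided 5% | 80% | 229.9 | 114.9 |
| One-sided 5% | 85% | 267.3 | 133.6 |
| One-sided 5% | 90% | 318.4 | 159.2 |
| One-sided 5% | 95% | 402.4 | 201.2 |
| Two-sided 5% | 80% | 291.8 | 145.9 |
| Two-sided 5% | 85% | 333.8 | 166.9 |
| Two-sided 5% | 90% | 390.7 | 195.3 |
| Two-sided 5% | 95% | 483.1 | 241.6 |
| Two-sided 2.5% | 90% | 461.4 | 230.7 |

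No 5% row gives 230 per group. The nearest is 241.6, which is 5% above. The last row does come out at about 231 per group: (2.241 + 1.282)² = 12.41, and 12.41 / 0.02690 = 461.4. That level is not stated in the article.

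**Step 3: read 0.7 and 0.5 as the two arms' event probabilities.** The mean is 0.6. HR 1.48 at two-sided 5% and 90% power then gives 10.507 / (0.25 × 0.6 × 0.1537) = 455.8 in total, or 227.9 per group, close to 230. But under proportional hazards these probabilities fix the hazard ratio:

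HR = ln(1 − 0.7) / ln(1 − 0.5) = ln 0.3 / ln 0.5 = 1.74

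That contradicts 1.48. With 1.74 (squared log 0.3049) the same settings give 10.507 / (0.25 × 0.6 × 0.3049) = 229.8, which is again a total.

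**Step 4: what the planned size delivers if pE is 0.7 and PA is the allocation share.** 460 × 0.7 = 322 events. Power = Φ(0.3920 × √(322/4) − z_α) = Φ(3.517 − z_α).

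- 460 patients: Φ(3.517 − 1.960) = 94% at two-sided 5%, and Φ(3.517 − 1.645) = 97% at one-sided 5%.
- 230 patients (161 events): 80% at one-sided 5%, 70% at two-sided 5%.
- Hazard ratio detectable with 322 events at two-sided 5% and 80% power: exp[2 × (1.960 + 0.842) / √322] = 1.37.

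**Step 5: drop-out.** 230 × 1.05 = 241.5, rounded to 242 as stated. To keep 230 after losing 5%, the number is 230 / 0.95 = 242.1, so 243 per group and 486 in total.

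**The case against.** The strongest reply is that the stated inputs yield no sample size until someone supplies a level, sidedness and power, and that one-sided 5% with 80% power is a back-fitted choice. This is correct, and it limits the point in four ways.

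- A reader might infer that the inputs themselves prove the doubling. They do not. Two-sided 2.5% with 90% power gives about 231 per group on the same formula. The article names two primary outcomes, so halving a 5% level would be an ordinary choice. The article states no such split, but it does not state one-sided 5% with 80% power either.
- A reader might infer that the trial is twice the size it needs. That holds only at one-sided 5% and 80% power. At two-sided 5%, 460 is 1.58 times the requirement at 80% power (460/292) and 1.18 times at 90% (460/391).
- A reader might infer a clash between a one-sided design and a two-sided analysis. The one-sided level comes only from the match in Step 1, not from the article, so no such contradiction can be charged to the plan.
- A reader might say that no α is given at all. The sample size section gives none, but the analysis section does state a 5% level.

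The reply does not remove the rest. At the only level the article gives, neither one-sided nor two-sided testing yields 230 per group at the four power values tried. The reading that comes close does so only with a hazard ratio and event rates that contradict each other. Nor is this detail that an article may leave to a fuller document: the article prints the inputs and the result, and they do not match.

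**Conclusion.** The point holds as a mismatch between stated inputs and stated result, with a probable explanation that needs confirmation. Reading pE as the overall event probability and PA as the allocation share, 230 is the total at one-sided 5% and 80% power, and totals at two-sided 5% run from 292 to 483 for 80 to 95% power. It is therefore probable that a total was labelled as per group. On the other reading, the event rates imply HR 1.74 against the stated 1.48.

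If the doubling occurred, the pre-drop-out target is 460 where the calculation supported 230. The consequence is a larger trial, not an underpowered one: about 94% power at two-sided 5% for HR 1.48. This rests on pE = 0.7, proportional hazards and a time-to-event comparison against a null hazard ratio of 1. The article does not confirm the last of these, since it calls the trial non-inferiority and the tests it lists are t, Wilcoxon and chi-square tests. The drop-out slip is minor: one patient per group.

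**What to change.** In Sample size calculation:

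1. Define θ, pE and PA.
2. State the endpoint, the hypothesis (reconciled with the non-inferiority label in Study design and with the listed tests), α, sidedness and power.
3. Check the PASS output, confirm whether 230 is the total or the per-group number, and restate the figure accordingly.
4. If 0.7 and 0.5 are the arms' event rates, reconcile them with the hazard ratio.
5. If 484 is kept and pE is the overall event probability of 0.7, say what it delivers: 460 evaluable patients (322 events) give about 94% power at two-sided 5% for HR 1.48, and 80% for HR 1.37. Present this as the power of the chosen size, not as its original basis.
6. Allow for drop-out by dividing: 230 / 0.95 = 243 per group, 486 in total, if 230 per group stands.

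The cost is rewording and one recalculation. No patients are added beyond the two from rounding drop-out correctly.
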